##### Study sample selection process

Within each centre, the target nurse will select:For the quantitative analyses:5 related professionals working inside the centre,5 related professionals working outside the centre,5 patients and their caregivers.For the qualitative analyses:10 related professionals working within the centre, including 5 professionals with regular contacts and 5 non-contact professionals (i.e. professionals with whom nurses should have contacts in the context of patient care but do not actually have any),10 related professionals working outside the centre (5 with regular contact ad 5 without any contact).

Within each centre, the non-target coordination nurses will select (for the quantitative study): 5 related professionals working inside the centre, 5 related professionals working outside the centre and 5 patients and their caregivers.

##### Study samples

Several samples will be constituted depending on the objective and type of study (qualitative and quantitative). We would expect 1148 observations divided into: 350 from qualitative study, 798 from quantitative study (Table 2):10 on-site observations (3 days in each centre, i.e. 30 days on-site observations) of target nurses2 focus groups1 “mono-professional” focus group with the ten target nurses (1 from each centre)1 “multi-stakeholders” focus group with a target nurse, related professionals (hospital and community-based), a patient and a caregiver338 individual interviews38 cancer coordination nurses (target and non-target nurses)10 to 20 professionals linked to a target coordination nurse in each centre5 of the patients followed by a target coordination nurse in each centre5 caregivers per centre (1 caregiver per patient)798 individuals interviewed by questionnaires38 cancer coordination nurses (target and non-target nurses)150 to 380 related professionals (5 to 10 related professionals per target and non-target nurses)190 patients (5 patients per cancer coordination nurses)190 caregivers (1 caregiver per patient)

**Table 2 Tab2:** EPOCK project data collection: Study population, sample size, data collection tools, indicators collected, France

Study population	Sample size	Data collection tool	Analysis results and Indicators collected
*Qualitative study (18 months)*			
Target cancer coordination nurses	10 nurses observations (3 days per nurse, per centre)	Structured on-site observations: quiet observation of daily work, during 3 days with an Ad hoc observation guide	Relevant components of reference operational framework of cancer care coordination interventions for the French health care system: - Structure of the coordination intervention (organisational rules, human, financial, material, perceived resources, representations, beliefs) - Actors of coordination (role, competences …) - Process of care coordination and propositions of results - Environment, contexts of coordination
Target cancer coordination nurses	1 (1 day for the 10 nurses)	“Mono-professionals” target nurses focus group	
A cancer coordination nurse, a medical oncologist, a general practitioner, a home nurse, a patient and his caregiver	1 (1 day in 1 centre)	“Multi-stakeholders” focus group	
Cancer coordination nurses	38 (target cancer coordination nurses [n = 10] and all the others selected by the investigation centres [*n* = 28])	All providers’ semi-structured interviews	
Referral professionals to cancer coordination nurses	200 (20 professionals selected by the 10 target cancer coordination nurses)		
Patients	50 (5 patients selected by the 10 target cancer coordination nurses)		
Patients’ caregivers	50 (1 caregiver per patient)		
*Quantitative analysis* ad hoc *survey (18 months)*			
All cancer coordination nurses	38 (target and non-target cancer coordination nurses)	Self-administered questionnaires	Socio-demographic data, perceptions of organisational conditions
		Eisenberger Survey of Perceived Organizational Support (SPOS) score	Perception that organisation contributes to their work well-being by an adequate organisational support
		Rizzo’s questionnaire	Role perceptions (measures of role conflict and ambiguity)
		The workplace commitment Allen and Meyer’s scale	Measures of affective commitment, normative commitment, and continuance commitment
Referral professionals to cancer coordination nurses	380 (10 professionals per cancer coordination nurses)	Ad hoc self-administrated questionnaire	Satisfaction with coordination of care
Patients	190 (5 patients per cancer coordination nurses)	Ad hoc self-administrated questionnaire	Satisfaction with coordination of care
		EPICES Social precariousness score	Measure of deprivation
		Quality of Life Questionnaire – Core 30	Score of overall health status and quality of life; score reflecting levels of function domains and levels of symptom burden
Patients‘caregivers	190 (1 caregiver per patient)	Ad hoc self-administrated questionnaire	Satisfaction with coordination of care
		Zarit burden inventory	Measure subjective caregiver burden (estimating the total hours per week spent doing things for patients and how many hours caregivers missed paid work in the prior month due to caregiving responsibilities)

Sample estimations relative to the quantitative analysis were made from literature reference data to ensure sufficient accuracy for the main validated scales studied.

### Data collected (Table 2)

#### Qualitative study

##### Daily quiet structured observations of target nurses (1 on-site target nurse observation during 3 days per centre, i.e. 10 observations).

The target nurses will be followed by a research psychologist throughout their working day and all their activities will be recorded. This will describe the actual work of the various target cancer coordination nurses selected for the study, particularly in terms of activity, interlocutors, tools used and time spent on tasks. This will allow a first capture of the most accessible elements of their professions, to identify the first similarities or differences in their activities, and can be linked to other qualitative measures. These preliminary structured observations will be useful for adapting qualitative and quantitative collection tools. One target nurse per centre will be observed to get an overview of the full heterogeneity of practices (i.e. 10 cancer coordination nurses who represent their professions in the various centres).

##### Semi-structured interviews will be performed among cancer coordinator nurses, referral professionals (hospital professionals, community healthcare workers), patients and their caregivers.

Semi-structured interview guides will be built in part from the areas of the care coordination framework already identified in the implementation phase (phase 1). They will be performed to identify invariants and variants of practices of the cancer care coordination nurses, to capture the representations and feelings related to this coordination of cancer care, while taking into account the point of view of the different stakeholders involved in this coordination. We plan to include 10 target cancer coordination nurses and 28 other cancer coordination nurses (non-target) identified in the 10 centres, which represent the different types of cancer care coordination nurses from the centres studied. We also wish to interview 20 referral professionals (health professionals, medico-social and administrative professionals) who work in collaboration with these nurses: 10 hospital-based professionals (5 professionals who have interaction with cancer coordinating nurses, and 5 professionals with no interaction when they should have one), 10 city-based professionals (5 with and 5 without interaction with cancer coordination nurses), in order to have the most complete possible experience from these actors, which are involved in the coordination of care. Finally, we will include patients followed by coordination nurses and a caregiver (where possible), to gather the experiences of the primary beneficiaries of cancer care coordination. We set this number at 5 patients and caregivers (1 caregiver per patient) per centre, to ensure sufficient number of different opinions and capture as many varied representations as possible from patients and their relatives. A total of 338 individual will be interviewed. However, the investigating psychologists will take into account the saturation of the discourse (on the themes and perceptions) in order to possibly reduce the number of interviews or to reduce the duration of the interviews.

*Focus Groups* will provide additional and undeveloped information following interviews and questionnaires on the role of each cancer coordinating nurse. We will conduct two subtypes of focus groups: a) a multi stakeholder’s focus group including hospital-based professionals (a target cancer coordination nurse, an oncologist, a clinical care nurse) and city-based ones (a general practitioner, an independent nurse, a pharmacist) with a patient and a caregiver’s: after having collected qualitative information from each actor separately, we will dynamically highlight the perceptions of the different actors involved in or concerned by cancer care coordination. Focus groups could assess the points of convergence or divergences relating to the missions of the cancer coordination nurses and stakeholders needs; b) A “mono-professional” focus group between target coordination nurses: it will concern all the target professionals identified in each centre (1 target nurse per centre, *n* = 10) and will allow a direct comparison of the similarities and differences between these new coordination nursing professions, allowing participants to share their experiences with each other and to compare it.

Saturation of themes will be used as a criterion for discontinuing data collection (Table 2).

*Quantitative study* will provide a quantified description and analysis of the psychosocial characteristics of these new professions, both in terms of organisation, perception and job attitudes of cancer coordination nurses, quality of life of patients, reduction of the burden on caregivers, but also in terms of satisfaction with the coordination intervention by all stakeholders involved in the intervention. Quantitative data collection mostly relies on international standardised scales and Ad hoc questionnaires among all providers.

Eisenberger Survey of Perceived organizational support score [57] will be used to measure the cancer coordination nurses’ perception concerning the extent to which the organisation values their contribution and cares about their well-being. The Meyer and Allen’s model [58, 59] proposes that organisational commitment is experienced by the employee as three simultaneous mind-sets encompassing affective, normative, and continuance organisational commitment. Affective commitment reflects commitment based on emotional ties the employee develops with the organisation primarily via positive work experiences. Normative commitment reflects commitment based on perceived obligation towards the organisation, for example rooted in the norms of reciprocity. Continuance Commitment reflects commitment based on the perceived costs, both economic and social, of leaving the organisation.

Among professionals working with cancer coordination nurses (referral professional), we will measure satisfaction of care coordination with an Ad Hoc questionnaire due to the lack of validated scale in French language. This questionnaire will be developed from a satisfaction survey conducted by the French National Cancer Institute and the French Ministry of Health [60].

The Quality of Life Questionnaire Core 30 items (version 3.0) from The European Organisation for Research and Treatment of Cancer (EORTC) [61] will be used to measure patient’s perceptions of the impact of their illness and treatments on their well-being. This questionnaire (appropriate for self-administration, *i.e* brief and easy to complete) is composed of 5 multi-item function scales (physical, role, cognitive, emotional, and social) and 9 symptom scales (fatigue, pain, and nausea and vomiting) and a number of single items assessing additional symptoms commonly reported by cancer patients (dyspnoea, loss of appetite, insomnia, constipation and diarrhoea) and perceived financial impact of the disease. The questionnaire is validated in its French version and is specific to cancer.

The Zarit burden inventory will be used to self-assess the material and emotional burden felt by caregivers [62]. It has been reported in caregivers of cancer patients [63, 64].

### Data collection process

The quantitative and qualitative data collections will be performed at the same time across the ten investigation centres located in five French regions.

Structured observations, semi-structured interviews and focus groups will be conducted by a team of research psychologists in all the ten centres.

All questionnaires will be collected within each centre, according to the same procedures. A project manager will coordinate data collection with a collection’s referent within each centre. This referent will be the health executive or the person designated by the head of the department or the principal investigator from the centre in which the coordination professional is located.

#### Data collection from all cancer care coordination nurses

Target and non-target nurses will be contacted directly by the project team to complete their questionnaires (self-administrated questionnaires). Questionnaires will be distributed in a sealed envelope by investigators to all coordination nurses in each centre (target and non-target coordination nurses). These nurses will have 2 weeks to answer the questionnaires (with several reminders by phone or email every 15 days over 3 months). Questionnaires will be returned directly to the project team at the promoter centre. Questionnaires will be enclosed in a sealed envelope with a label containing an anonymous identification number previously established by the study’s project manager and the data manager. This professional’s identification number will not be known by the department’s health officer.

#### Data collection from professionals (hospital and city) related to coordination nurses

Cancer nurse coordinators (target and non-target) will identify their related professional (5 professional working inside the centre, and 5 outside). After obtaining their agreement, the Epock project manager will send self-questionnaires to these professionals with a prepaid reply envelope. They will have 3 weeks to answer. The Epock project manager will at last contact them by telephone to retrieve their questionnaires (two telephone reminders at two-week intervals, then a reminder at 2 months, and a final mailing at 3 month).

#### Data collection from patients and caregivers

Coordination nurses will have to select patients and their caregivers by handing them self-administrated questionnaires. Patients and their caregivers’ will complete self-questionnaires before or after the nursing time support with the coordinating nurse. Patients will return their questionnaires to nurses, and nurses to the promoter. Patients and caregivers could also return their questionnaires directly to the project team using a prepaid envelope.

In addition, for the 5 patients identified by coordination nurses in each centre, the coordination nurses will complete an anonymous questionnaire containing data on age, individual deprivation (with the French “Evaluation of Deprivation and Inequalities in Health Examination Centres” score-the EPICES score) [65], type of primary tumour (International statistical Classification of Diseases and Related Health Problems 10th Revision, in French language) [66], stage of the disease (with the Tumor-Node-Metastasis [TNM] classification of malignant tumours) [67] at the time of management by the coordination nurse. The coordination nurses will be responsible for following up with patients and caregivers to retrieve their questionnaires.

The EPOCK study protocol was approved by institutional review boards and Ethics Committees (Comité de Protection des Personnes [CPP] du Sud-Ouest et Outre-Mer III number: 2017-A02049–44).

The investigator or the coordination nurse targeted by centre offers to participate in this research to the participant / legal representative. He informs him of the purpose, the computerised processing of his data will be collected during this research and also specifies his rights of access, opposition and rectification to these data. Information notes will be given to patients, their relatives and the healthcare professionals requested. The investigator or coordinating nurse will also check the eligibility criteria. If the person agrees to participate, he or she gives his or her consent orally. In case of participation agreement is collected from the representative, the participant will be informed as soon as possible and asked for his or her participation agreement for the possible continuation of this research and for the use of the data concerning him or her that are collected in the context of this research. The participant may, at any time, object to the use of his or her data for research purposes.

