***O****rale”)* specialised nurses in oral chemotherapy,The “**IDE HAD-CAD”**
*(“****I****nfirmier coordonnateur d’****H****ospitalisation*
***A D****omicile pour les*
***C****himiothérapies*
***A D****omicile”)* coordinating nurse specialised in Hospital Care at Home for intravenous chemotherapy at home.**Centres.** We select all types of health care facilities existing in France: university or non-university centres, public or private, comprehensive cancer centres, and hospital care at home (HAD), in urban or rural areas, regardless of their size (large, medium and small centres). A total of ten centres were selected from five French regions because each of them has implemented a subtype of target cancer coordination nurse (Table 1). We will thus exclude: the PTAs (integrated platform for professionals facilitating patient’s orientation and professional’s coordination) that have been recently designed at a national level and implanted at a local level because they don’t coordinate from the hospital to the city, the healthcare and social service networks, private home-based care providers and healthcare houses.**Non-target cancer coordination nurses**. They will be identified by each centre in addition to the target nurses. They represent all the coordination nurses implemented in each selected centre. Won’t be involved other professions of cancer coordinators: coordinating medical doctors from care networks, coordinating medical doctors from hospital care at home, practitioners from centres for cancer care coordination (the French 3Cs), practitioners from French regional cancer networks. Nevertheless, these coordinators will be included as “referral professionals” to cancer coordination nurses (target and non-target).“**Referral professionals”** to cancer coordination nurses working inside the selected centre (hospital professionals: medical [oncologists, radiotherapists, surgeons]; paramedical [nurses, health officers], administrative [medical secretary, medical-administrative assistant], supportive oncological care [social worker, psychologist, dietician, physiotherapist ...], patient associations…) and outside (primary care providers and home care workers) who have activities related to cancer coordination nurses. They will be identified by target and non-target nurses.**Patients** with a pathway coordinated by a target nurse: adult patients with any types of cancer at any stages, who have been coordinated in the last month or have had at least 2 contacts with the cancer care coordinator nurse (patient-cancer care coordinator nurse pairs). Patients will be selected by target and non-target nurses already included in the Epock study (5 patients per coordination nurses).**Caregivers** chosen by patients already selected (patient-caregiver pairs): one caregiver per patient. If the patient is isolated, no relatives will be included.

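### Nurses choose the patients who rate their own coordination and handle the forms, so patient and caregiver satisfaction is likely biased upward by an unknown amount

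*Protocol article*

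**What the plan says.** **Patients.** The Population section states "Patients will be selected by target and non-target nurses already included in the Epock study (5 patients per coordination nurses" per nurse. Eligibility requires coordination within the past month or two or more contacts with the nurse. Nothing says which five of the eligible patients are taken.

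The section on data collection from patients and caregivers adds "Coordination nurses will have to select patients and their caregivers by handing them self-administrated questionnaires", with completion either before or after the session with that nurse. On return it says "Patients will return their questionnaires to nurses, and nurses to the promoter", and then "Patients and caregivers could also return their questionnaires directly to the project team using a prepaid envelope". On reminders it says "The coordination nurses will be responsible for following up with patients and caregivers to retrieve their questionnaires".

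**Caregivers.** The Population section describes them as "chosen by patients already selected (patient-caregiver pairs): one caregiver per patient". The data collection section (the hand-out sentence above) and the Study sample selection process section have the nurse select patients together with their caregivers.

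**Professionals.** "Cancer nurse coordinators (target and non-target) will identify their related professional (5 professional working inside the centre, and 5 outside". The project manager then posts the forms with a prepaid reply envelope and makes the reminders.

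**Nurses' own forms.** These travel in sealed envelopes, and "Questionnaires will be returned directly to the project team at the promoter centre".

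**Use of the data.** The Analysis section relates contextual factors to the satisfaction of patients, caregivers and referral professionals.

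**The concern.** For patients, one person is the subject of the rating, chooses the raters, hands over the form, may take it back completed and chases it if it is late. Two mechanisms follow. A nurse free to choose may, without intending it, favour patients with whom the work went well. A patient still in that nurse's care may soften a form that returns through the nurse's hands. Both push satisfaction the same way.

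Two uses of the data are exposed: the reported level of satisfaction, and the associations between satisfaction and context. The second suffers if nurses or settings differ in how strongly they select. The plan describes no record of the eligible patients who were not approached, so the strength of selection could not be checked later.

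**Working it through.** **1. Counts (Study samples section and Table 2).** 38 nurses + 38 × 10 = 380 professionals + 38 × 5 = 190 patients + 190 caregivers = 798, the plan's own questionnaire total. Removing the 38 nurses leaves 760 satisfaction raters.

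**2. The nurse's role, by group of raters.**

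| Step | Patients (190) | Caregivers (190) | Professionals (380) |
|---|---|---|---|
| Chooses the rater | Nurse | Patient or nurse (text conflicts) | Nurse |
| Hands out or sends | Nurse | Nurse | Project manager |
| Return | Nurse, or optional prepaid envelope | Optional prepaid envelope; nurse route is stated for patients | Prepaid envelope |
| Reminders | Nurse | Nurse | Project manager |

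Nurse hand-out and follow-up apply to 190 + 190 = 380 of 760 (50%). The nurse directly names 380 + 190 = 570 of 760 (75%), if patients choose the caregivers.

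**3. Possible shift in a proportion (assumed inputs).** The documents give no satisfaction level and no selection strength. Let p be the true proportion satisfied and k the factor by which a satisfied patient is more likely to be picked. The sample then shows pk / (pk + 1 − p). With p = 0.70:

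- k = 1: 70% (no bias)
- k = 1.5: 1.05 / 1.35 = 77.8%
- k = 2: 1.40 / 1.70 = 82.4%
- k = 3: 2.10 / 2.40 = 87.5%

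The bias is about +8 to +18 points. For scale, the 95% half-width at n = 190 is 1.96 × √(0.21/190) = 6.5 points if patients are independent. They come five per nurse. With an assumed intraclass correlation of 0.1 or 0.2 the design effect is 1 + 4 × 0.1 = 1.4 or 1 + 4 × 0.2 = 1.8, and the half-width is 7.7 or 8.7 points. The mildest scenario is then no larger than sampling error.

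**4. Possible shift in a score (assumed inputs).** Let the nurse approach a share q of eligible patients, with correlation ρ between the nurse's choice and satisfaction. With c the normal cut-off for q and λ = φ(c)/q, the mean shifts by ρλ SD and the SD is multiplied by √(1 − ρ²λ(λ − c)).

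| q | ρ | Mean shift | SD multiplied by |
|---|---|---|---|
| any | 0 | 0 | 1.00 |
| 0.5 | 0.2 | +0.16 SD | 0.99 |
| 0.5 | 0.5 | +0.40 SD | 0.92 |
| 0.25 | 0.5 | +0.64 SD | 0.90 |
| 0.25 | 0.8 | +1.02 SD | 0.72 |

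The upward shift is the clearer effect. Loss of spread is small unless selection is strong or the scale has a ceiling.

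**5. Effect on associations.** The formula in step 3 multiplies the odds of satisfaction by k.

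- *Same k everywhere:* true rates of 60% and 80% (odds 1.5 and 4, odds ratio 2.67) appear at k = 2 as 75% and 88.9% (odds 3 and 8, odds ratio 2.67). The gap narrows from 20 to 14 points, but the odds ratio is unchanged.
- *Different k:* two contexts with the same true 70%, one with k = 1 and the other with k = 2, appear as 70% and 82.4%. The odds are 2.33 and 4.67, a spurious odds ratio of 2.

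**The case against.** The strongest reply is that satisfaction is peripheral and partly protected. The main objective is to evaluate nurses' practices and working context against a framework. The Strengths and limitations section says the quantitative part serves mainly to capture the nurses' own perceptions, and those forms go straight to the project team. On-site observation, interviews led by psychologists (including professionals who should have had contact but did not) and triangulation reduce reliance on the satisfaction questionnaire. This stands, and it limits the consequences. It does not change how the five patients are chosen.

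The prepaid envelope is already offered to patients and caregivers. That eases the return step for those who use it, but not selection, hand-out or follow-up.

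A reader might infer three stronger things that the documents do not support:

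- *That the nurse handles every rater's forms.* For professionals, half of the planned raters, the nurse only names them.
- *That satisfaction is known to be inflated and its spread compressed.* No satisfaction data, pool size or selection strength is given. With no selection on satisfaction and no courtesy effect, both are zero.
- *That no analysis can rescue the associations.* Under a constant selection factor, odds ratios survive, and logistic or polytomous regression is the planned adjusted analysis. Distortion needs selection that varies between nurses or contexts.

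Finally, the Monitoring and coordination section says data are still being collected, so a change now mixes two procedures. That is a real cost.

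**Conclusion.** The concern holds for patients, and for caregivers as regards hand-out and follow-up. For professionals it is confined to the choice of rater. Patient and caregiver satisfaction is likely biased upward. The size cannot be estimated from the documents; +8 to +18 points rests wholly on an assumed true level of 70% and assumed selection factors of 1.5 to 3. Associations with context are distorted if the strength of selection differs between nurses or contexts, which the procedure does nothing to prevent.

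The conflict over who chooses the caregiver is in the text itself and needs reconciling. The practice observations and the nurses' own scales are not affected by this point.

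**What to change.** **For the remaining collection**

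- Each nurse or centre referent lists the patients who meet the existing criteria and takes five consecutively from a random or fixed start date.
- Apply a similar list-based rule to the internal and external professionals where feasible.
- Make the existing prepaid envelope to the project team, sealed by the respondent, the only return route for patients and caregivers.
- Fix one completion moment relative to the nurse session.
- Have reminders come from the centre referent or project manager where contact details and consent allow. Consent is oral, at the time participation is offered, so passing on contact details would have to be covered there.
- State in one place who chooses the caregiver.

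**For data already collected**

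Record how each patient was selected and by which route the form came back, compare results before and after the change, and state the limitation in the report.

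**Cost**

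One list per nurse, postage, a possibly lower response rate, and two sampling regimes within one study. The prepaid envelopes already exist in the plan.
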